#### Analysis

##### Validation of prognostic model

The prognostic model developed in the IPD will be externally validated using data collected in the prospective cohort data, using the measures of discrimination and calibration described in QUIDS Protocol part 1,^1^ including R^2^, C statistic, calibration slope, calibration in the large and calibration plots of observed versus predicted risks across deciles (with Loess smoother). The average performance of the model will be summarised across the centres in the cohort study. Between-centre heterogeneity in performance will also be summarised, and reduced (if necessary) by recalibration techniques regarding the strategy for the choice of baseline risk (intercept). That is, the predictor effects will not be modified from the IPD meta-analysis model, but the intercept may need to be tailored to improve validation in UK centres (eg, for rural settings). Based on the findings, a final model and its implementation strategy will then be recommended for use.

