**Figure 1 F1:**
[figure not shown]
Flow chart illustrating the design of QUIDS study and conceptual division into part 1 and part 2. qfFN, quantitative fetal fibronectin.

In QUIDS Protocol part 1, we have described how we will perform (1) an individual participant data (IPD) meta-analysis and (2) and economic analysis. The protocol details how we will develop and internally validate a prognostic model using quantitative fFN (as a continuous variable) and other risk (prognostic) factors and to evaluate the added value of quantitative fFN towards this prognostic model performance. We will also provide an economic rationale for the prognostic model and analyse its cost-effectiveness from the perspective of the National Health Service (NHS).

In this, the QUIDS Protocol part 2, we will detail the prospective cohort study to externally validate and, if necessary, refine the prognostic model. This will be performed in at least eight UK hospitals with different settings (rural/urban) and different levels of neonatal care facilities. In addition, acceptability of quantitative fFN testing, and effects on maternal anxiety will be performed. We will assess the potential cost-effectiveness of the final prognostic model/decision support tool. This additional analysis will allow us to model the full costs and effect impacts of the different prognostic model and compare these in a cost-effectiveness analysis to provide an evidence-based economic rationale for implementing the diagnostic tool in the NHS.

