#### Decision support

We will develop a decision support tool in accordance with the guidelines produced by the International Patient Decision Aid Standards Collaboration.^21^ Scoping of decisional requirements and how data should be presented was performed during focus group consultation as part of QUIDS Qualitative (online supplementary material). A prototype decision support tool incorporating the initial prognostic model, developed as part of the IPD meta-analysis, will be tested with women and clinicians, as part of the acceptability studies described above. A final version will be updated with the validated (and, if necessary revised) prognostic model generated from the prospective cohort study. The multidisciplinary trial steering committee (TSC) will oversee the development process, and decide how material is selected for inclusion.

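### The plan measures the calibration slope but lets only the intercept be updated, so it has no way to correct predicted risks that are too extreme or too moderate before a final model is recommended

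*Protocol article*

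**What the plan says.** The Validation of prognostic model section of the Protocol article lists R², "C statistic, calibration slope, calibration in the large and calibration plots of observed versus predicted risks across deciles". It then says that between-centre heterogeneity in performance will be reduced, where needed, by "recalibration techniques regarding the strategy for the choice of baseline risk (intercept"), and explains this by stating that "the predictor effects will not be modified from the IPD meta-analysis model, but the intercept may need to be tailored to improve validation". The section closes by saying that, on the basis of the findings, "a final model and its implementation strategy will then be recommended for use". It ties no action to a slope that differs from 1.

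Two other places use wider language. Aims and methodologies (text after Figure 1) gives the cohort's purpose as "to externally validate and, if necessary, refine the prognostic model". Decision support says that the final tool will take up the "validated (and, if necessary revised) prognostic model generated from the prospective cohort study".

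The Abstract says the final validated model will be presented as a mobile or web application. Patient and public involvement says women and clinicians want it to show the 7-day risk. Ethics and dissemination links the expected benefit to ruling out preterm delivery.

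**The concern.** Calibration in the large and the calibration slope describe different faults. The first asks whether the average predicted risk is right, the second whether predictions are spread too widely (slope below 1) or too narrowly (slope above 1). Changing the intercept can repair the first fault only. A common multiplier on the linear predictor would repair the second, but it changes every predictor effect and so falls under the stated prohibition.

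The tool is meant to show an absolute risk and to be useful for ruling out delivery, so calibration at the low end carries most of its value. A slope below 1 followed by intercept-only updating would leave the average correct while women with low displayed risks were shown figures that are too low. The cohort would reveal the fault, and the stated update rule could not remove it.

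**Working it through.** **1. The plan's own figures.** Statistics and sample size calculation: 1600 × 0.06 = 96 events and 1600 × 0.12 = 192 events; 36 000 × 0.089 × 0.5 = 1602 recruits; 60 minimum events ÷ 10 per covariate = 6 covariates. All reproduce.

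**2. Inputs for the check.**
- From the article: event rate 6% to 12%, n = 1600, minimum 60 events.
- Assumed, because the article does not give them: a normally distributed linear predictor with SD 1.0 to 2.0 (C statistic about 0.75 to 0.89 if the slope is 1), and a true slope of 0.7, 0.8 or 0.9.

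**3. Method.** Let z be the standardised linear predictor, s its SD and k the true slope.
- Displayed risk after a perfect intercept update: expit(a + s·z), with a chosen so that the mean equals the event rate.
- True risk: expit(b + k·s·z), with b chosen so that the mean equals the same event rate.
- A woman shown risk p therefore has true log-odds b + k·(logit p − a).

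**4. One case in full.** Event rate 6%, s = 1.45, k = 0.7 gives a = −3.569 and b = −3.178. For a displayed 1%, logit(0.01) = −4.595. True log-odds = −3.178 + 0.7 × (−4.595 + 3.569) = −3.896, a true risk of 2.0%. In the same case:
- Women shown under 2% (41% of the cohort) average 0.9% displayed and 1.8% true.
- Women shown over 30% average 43% displayed and 30% true.

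**5. True risk behind a displayed 1%, across SD 1.0 to 2.0 and event rates of 6% to 12%.**

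| True slope | True risk |
|---|---|
| 0.7 | 1.9% to 2.5% |
| 0.8 | 1.5% to 1.9% |
| 0.9 | 1.2% to 1.4% |
| 1.2 | 0.5% to 0.6% (error reversed) |

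The direction does not depend on the assumed SD. Average calibration is exact in every row.

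**6. With one common multiplier added.** If intercept and slope are both re-estimated, displayed and true risk agree throughout this model, and the predictors keep their weights relative to one another.

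**7. Can the cohort estimate the slope?** From the Fisher information, at true slope 0.8 the SE of the slope is about 0.06 to 0.11 with 1600 women and 0.09 to 0.15 with 60 events (60 ÷ 0.06 = 1000 women, or 60 ÷ 0.12 = 500). So yes. A rule that acts only when the 95% CI excludes 1 is weaker. At slope 0.8 it fires about 43% to 94% of the time with 1600 women, and about 26% to 59% with 60 events. At slope 0.7 with 1600 women, 6% events and SD 1.45 (SE 0.082) it fires about 96% of the time, but that is a favourable case: with SD 1.0 it is 77%.

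**The case against.** **Fixed effects are a defensible choice.** They keep the cohort a true external test of the part 1 model, and a slope-updated model would have no independent validation here. This stands as a cost of the fix. It does not argue against reporting the un-updated model first and the updated versions afterwards.

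**The restriction may cover only between-centre heterogeneity.** The sentence explains that step, so the article could be read as silent on a poor overall slope, with detail left to the full protocol. The wording is ambiguous to that extent. But the statement that predictor effects will not be modified carries no qualification, and no other update route is named.

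**The harm is conditional.** The assumed SD and slope are not in the article. Internal validation belongs to part 1, whose protocol is not shown, and any shrinkage there would make a low slope less likely. At slope 0.9 the error is small. All of this stands. None of it supplies a remedy if the cohort does show a slope away from 1.

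**Two stronger readings are tempting and not supported.**
- A reader might infer that the article contradicts itself by promising to refine or revise the model. An intercept change is itself a refinement, and both passages say it will be done only if necessary. They are broader than the analysis section, without strictly contradicting it.
- A reader might infer that a miscalibrated model would certainly reach the app. The recommendation is to be based on the findings, the steering committee oversees development of the tool, and the benefit is stated conditionally. No rule for withholding the model is given, but neither is unconditional release.

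**Conclusion.** The point holds as a gap in the update rule. The plan measures the slope and fixes in advance a form of recalibration that cannot respond to it. If the slope is not 1, displayed risks stay wrong at both ends even when the average is right. For a displayed 1%, the true risk would be about 1.9% to 2.5% at slope 0.7, falling to 1.2% to 1.4% at slope 0.9. These sizes rest on the normal linear-predictor model and the assumed SDs and slopes, together with the article's 6% to 12% event rates. They show what would follow from a given slope and do not predict which slope will occur. The point should be addressed before the cohort is analysed. It is a missing correction step and does not show that the final model will be wrong.

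**What to change.** Amend the validation section as follows.

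1. Report the un-updated part 1 model first, as the external validation.
2. Keep the relative predictor weights fixed, and pre-specify two updated versions: intercept only, and logistic recalibration with a new intercept plus one common multiplier of the linear predictor. Report all three.
3. Choose between the updated versions on the slope estimate with its CI and on calibration in the low-risk range. Do not rely only on whether the CI excludes 1, given its limited power.
4. State what happens to the recommendation if low-risk calibration stays poor.
5. Align the wording in Aims and methodologies and in Decision support with the updating that is actually permitted.

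The cost is a few sentences and one extra estimated parameter, with no new data. The drawback is that the updated model has no independent validation within this study, and the report should say so.

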##### Economic analysis

The economic model will be refined, integrated and updated with data from the prospective study cohort, so as the most up to date and validated evidence is used to inform a cost-effectiveness decision. Such an iterative approach to economic evaluation is now well established.^14 15^ The care pathway following diagnosis will be included in the economic analysis, using data from the cohort study such as the diagnostic test accuracy data, resource use data (ie, steroid use, other medications, time in hospital, hospital transfer) and secondary outcome data (ie, treatment of side effects, morbidity, mortality) so as to capture the full costs and effect impacts (quality of life, morbidity and mortality) for both the mother and baby. Resource use data will be combined with unit cost information from the British National Formulary^16^ and NHS reference costs.^17 18^ Outcomes will be reported as the incremental cost per correct diagnosis, and incremental cost per quality-adjusted life year gained of the qfFN prognostic model compared with current practice (no qualitative fFN model). The analysis will adhere to the National Institute for Health and Care Excellence reference case and the recommended guidelines for decision modelling and reporting of economic analyses.^18^ Probabilistic sensitivity analysis will be undertaken to explore how uncertainty in the model inputs impact on the cost-effectiveness outcome.^19^

##### Acceptability of fFN testing and effects on anxiety

Maternal anxiety will be measured before and after quantitative fFN testing using the validated STAI. The STAI Form Y is a widely used tool for measuring both temporary ‘state anxiety’ and the more general, long-standing ‘trait anxiety’. The STAI is designed for the self-reported assessment of the intensity of feelings of apprehension, tension, nervousness and worry. STAI-Anxiety scores increase in response to physical danger and psychological stress, making it highly appropriate for this study. The use of STAI in pregnancy studies is discussed by Hundley *et al* and we will interpret the results accordingly.^20^

The questionnaire will be administered prior to fFN testing (baseline) and 24–48 hours after the test, to assess early reactions to the test and any acute anxiety prompted by the result of the test. We will also be able to assess any differences in those presented with a high-risk or low-risk result. Although it might be interesting to assess anxiety again in the latter stages of pregnancy, it is likely that, in this population, many pregnancies will not reach full term. Thus, we believe our strategy of repeat questionnaire administration will allow measurement of longer-term anxiety induced or alleviated by the test, while minimising bias due to preterm or term delivery itself or loss to follow-up.

Follow-up interviews will be performed with a subgroup of participants (n=30) to enable deeper exploration of women’s views regarding fFN testing, to gain insight into the rationale for responses given in the questionnaires. Interviews will be conducted following confirmation of pregnancy status. Acceptability of the prognostic model will also be assessed with women and a group of clinicians. All interviews will be audio recorded with consent, and field notes taken to ensure an audit trail.

#### Decision support

We will develop a decision support tool in accordance with the guidelines produced by the International Patient Decision Aid Standards Collaboration.^21^ Scoping of decisional requirements and how data should be presented was performed during focus group consultation as part of QUIDS Qualitative (online supplementary material). A prototype decision support tool incorporating the initial prognostic model, developed as part of the IPD meta-analysis, will be tested with women and clinicians, as part of the acceptability studies described above. A final version will be updated with the validated (and, if necessary revised) prognostic model generated from the prospective cohort study. The multidisciplinary trial steering committee (TSC) will oversee the development process, and decide how material is selected for inclusion.

### Trial management and oversight arrangements

#### Project management group

The trial will be coordinated by a project management group (PMG), consisting of the grant holders (chief investigator and coapplicants), the trial manager, representatives from the Study Office and CHaRT (the supporting Clinical Trials Unit (CTU)), plus service user representatives (PAG). The PMG will meet approximately every 4 months by teleconference or face to face.

The trial manager based in Edinburgh will oversee the study and will be accountable to the chief investigator. The trial manager supported by the trial administrator(s) will take responsibility for the day-to-day transaction of study activities. They will be supported by the CTU at CHaRT to provide expertise and guidance. The trial manager will be responsible for checking the CRFs for completeness, plausibility and consistency. Any queries will be resolved by the investigator or delegated member of the trial team.

A Delegation Log will be prepared for each site, detailing the responsibilities of each member of staff working on the trial.

#### TSC and data monitoring committee

A combined TSC and data monitoring committee (DMC) will oversee the conduct and progress of the trial. The terms of reference of the Committee will be developed separately. Members of the TSC/DMC will consist of experts and two patient representatives.

## Patient and public involvement

Patient representatives were consulted during the protocol development and have been invited to join the PMG and the TSC, and will thus be involved in the recruitment to, and conduct of, the study. Coauthor [name] is a patient representative. Prior to commencing QUIDS, we performed a qualitative study to determine the decisional needs of pregnant women with signs and symptoms of preterm labour, their partners and their caregivers. This is described in the separate protocol ‘QUIDS Qualitative’ (online supplementary material). The end product of QUIDS will be a decision support aid to help clinicians, women and their partners decide on management of threatened preterm labour, based on the results of the quantitative fFN. In QUIDS Qualitative women and clinicians indicated that they would prefer this to be on web-based or mobile app-based format, presenting the risk of preterm birth within 7 days of testing. Social media will be used to signpost publications and conference presentations and highlight important findings. Twitter and Facebook will be used to disseminate findings to professional organisations, charities, stakeholders and the public. Communication to the general public will further be facilitated by our close links with charities such as Tommys.^22^

## Ethics and dissemination

The study will be conducted in accordance with the principles of Good Clinical Practice (GCP). Local research and development approvals will be obtained prior to commencement of the study at each site.

On completion of the study, the study data will be analysed and tabulated, and a clinical study report will be prepared in accordance with GCP guidelines. Results will be communicated to the academic community via the scientific literature, attendance at conferences and invited presentations. Summaries of results will also be made available to investigators for dissemination within clinics. We anticipate that the decision support will be made available as web-based application that will be made freely available, so clinicians can access it easily and it can be readily translatable into UK practice. If it is found to be effective in ruling out preterm delivery, it is likely that it will decrease unnecessary costly, and potentially harmful treatments in women who have symptoms suggestive of preterm labour but do not deliver early.

### How patients are involved in this study

Patient representatives were consulted during the protocol development and have been invited to join the PMG and the TSC. Prior to commencing QUIDS, we performed a qualitative study to determine the decisional needs of pregnant women with signs and symptoms of preterm labour, their partners and their caregivers. This is described in the separate protocol “QUIDS Qualitative” (online supplementary material). The end product of QUIDS will be a decision support aid to help clinicians, women and their partners decide on management of threatened preterm labour, based on the results of the quantitative fFN. In QUIDS Qualitative, women and clinicians indicated that they would prefer this to be on web-based or mobile app-based format, presenting the risk of preterm birth within 7 days of testing.
